#### Data collection

An electronic case report form (eCRF) will be used to collect all study data. Only authorised personnel will be able to make entries, amendments or changes to patient data on the eCRF. The trial dataset will be held and analysed by the Glasgow CTU. Investigators will not have access to the full dataset until the trial is closed.

### Study timeline

#### Baseline assessments

The CYCLE-HD study protocol timeline is shown in Fig. 1. Baseline assessments will be undertaken on a non-dialysis day at the NIHR-Leicester Cardiovascular BRU.

**Fig. 1 Fig1:**
[figure not shown]
CYCLE HD study protocol timeline

#### Cardiac MRI

The CMR scan protocol timeline in shown in Fig. 2. Patients will be imaged on a 3 Tesla (3 T) CMR platform (Skyra, Siemens Medical Imaging, Erlangen, Germany). The CMR protocol will be similar to that previously described but without contrast administration [46]. LV volumes and mass will be quantified with epicardial and endocardial contours of a contiguous stack of multiphase ventricular short axis cines (10–12 slices, 8 mm slice thickness, 25 % gap) at end-diastole and end-systole. Native T1 and T2 mapping at mid-ventricular level will be undertaken for tissue characterisation, with non-contrast T1 mapping offering the opportunity to assess myocardial fibrosis [47, 48]. Vasodilator stress with adenosine at an initial dose of 140 μg/kg/min for three minutes will be given and myocardial perfusion will be assessed with the response in signal intensity on T1 and T2 maps compared to baseline [49]. Adequate haemodynamic response is assessed by either ≥10 % heart rate increase or ≥10 mmHg decrease in systolic blood pressure. Adenosine dose may be increased incrementally to an upper limit of 210 μg/kg/min to achieve haemodynamic response if needed. Feature tracking and/or tissue tracking will be used to assess systolic strain and diastolic strain rate [44]. Myocardial perfusion reserve (the ratio of global myocardial blood flow at rest versus stress) will be assessed using phase contrast velocity mapping of the coronary sinus before and after adenosine stress [50]. Aortic compliance will be assessed by measuring distensibility of the ascending and descending thoracic aorta. Changes in the cross-sectional luminal area of aorta in a 5 mm thick slice will be measured and concomitant measurement of blood pressure at the time of sequence acquisition will allow calculation of aortic distensibilty and pulse wave velocity [41]. Three point Dixon images for quantification of thoracic visceral fat content will be acquired in patients who tolerate the scan well.

**Fig. 2 Fig2:**
[figure not shown]
Cardiac MRI Protocol. (4/3/2C, 4/3/2 Chamber; LV, Left Ventricular; SA, Short Axis)

#### Echocardiography

Patients will be scanned by an accredited sonographer on a Phillips iE33 platform (Best, The Netherlands) in the NIHR-Leicester Cardiovascular BRU. Assessments will include: LV size and function; LV mass; relative wall thickness and geometry as per the American society of echocardiography guidelines [47]. In addition specific focus will be paid to diastolic dysfunction and end-diastolic integrated backscatter measurements that are directly related to the presence of myocardial fibrosis and validated in HD patients [51–55]. These data are key to assessing the long term effect of exercise on myocardial fibrosis in HD patients as the use of late gadolinium enhancement on CMR is not possible due to the risk of nephrogenic systemic fibrosis [56]. Speckle tracking for strain assessment will be also be undertaken.

#### Holter monitor

Patients will undertake 48 h Holter monitoring (Schiller, medilog®AR12 plus/AR4 plus/FD5 plus, Baar, Switzerland) that will start before dialysis and terminate just before the subsequent dialysis treatment 48 h later. In a sub-study, the intervention group will undergo a further 48 h Holter recording that will start before a dialysis session and includes the cycling exercise intervention and continues for the same time period afterwards. This will enable interim analysis to ensure that there are no adverse rhythm disturbances associated with exercise in the intervention group.

#### Non-Invasive Cardiac Output Monitor (NICOM)

Patients will have cardiovascular parameters measured by bioreactance prior to dialysis, using the NICOM (Cheetah Medical, Maidenhead, UK) in-line with their guidelines for use. This device assesses phase shifts in transthoracic voltage when a high frequency current is applied across the torso [57]. From this validated technique [58, 59] the NICOM provides readings of cardiac output, stroke volume, heart rate, total peripheral resistance, cardiac power and ventricular ejection time.

#### Blood sampling

Blood samples will be collected from the arterial needle before dialysis. Thirty millilitres will be collected to be centrifugated at 20 °C at 2500 × *g* for 15 min. Plasma will then be pipetted into cryotubes and frozen at -80 °C in an electronically monitored freezer for analysis in batches throughout the study. All samples will be collected, stored and disposed of in accordance with the Codes of Practice as laid out by the Human Tissue Authority.

#### Physical function tests

Patient physical functioning will be assessed by the shuttle walk tests, the sit-to-stand-60 (STS60) test and the short physical performance battery, all of which have been used extensively as accurate measures of aerobic capacity, lower leg strength and physical function in HD patients [60–62].

#### Anthropometric measures

Patients will have measures of hip and waist circumferences, body weight and body composition. Body composition will be analysed prior to dialysis, using bioimpedance spectroscopy (BIS). For this we will use the Body Composition Monitor (BCM Fresenius Medical Care, Bad Homburg, Germany), validated for use in HD patients [63], allowing for interpretation of normally hydrated lean and adipose tissues as well as excess fluid [64, 65] and other variables.

#### Quality of life and physical function

Patients will complete the following questionnaires to capture data about physical activity and quality of life: Short form-12 version 2 (SF-12) which has physical and mental component scores; the EQ-5D-5L which provides a functional index value and visual analogue score; the Palliative Outcome Scale–Symptoms Renal (POS-S Renal) to assess symptom burden; The Hospital Anxiety and Depression Scale (HADS) to assess anxiety and depression levels; The Leicester Dialysis Patients–Physical Activity Questionnaire (LDP-PAQ), which assesses perceived physical activity, perceived stage of change, perceived self-efficacy, self-reported physical activity levels and perceived barriers to exercise participation. Objective data on patient physical activity levels will also be gained from tri-axial accelerometers (Sensewear; BodyMedia, Inc. Pittsburgh, PA), which will calculate steps taken, energy expenditure (kcALs) and average metabolic equivalents (METS).

#### Collection of routine clinical information

As part of routine clinical care, a number of parameters will be collected on a monthly basis. These include (but are not limited to) blood pressure, weight and fluid removal for every dialysis session as well as biochemical and haematological blood tests.

#### Follow-up assessments

Follow up visits are summarised in Fig. 1. A one-month run-in period allows the exercise group to familiarise themselves with intradialytic cycling. Three months after this run in period (four months from baseline), interim assessments will be conducted. This will involve all baseline assessments except the CMR, echocardiogram and NICOM. The control group will also undergo interim assessments at month four.

Final assessments will be conducted for both exercise and control groups after seven months. Assessments at study completion will be identical to the baseline visit.

Following study completion, patients will be offered the opportunity to continue with intradialytic cycling if they wish and control patients will be offered the chance to move to a shift where exercise intervention is available. We will also ask patients to complete a feedback and evaluation form for ongoing development of study and future service provision.

#### Sub-study

Additional informed consent will be sought after the first CMR scan for ten control patients to be re-scanned using an identical scan protocol to assess inter and intra-observer variability and reproducibility of all scan parameters.

#### Investigation reporting

Cardiac imaging will not be reported until after the patient has completed the study so as not to influence the study outcome. However life-threatening incidental findings identified during scan acquisition will be reported to the chief investigator, the data safety management board (DSMB) and the sponsor, and a full report will be issued to aid clinical care and ensure patient safety.

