### Participant identification and recruitment

Prevalent adult patients undergoing in-centre maintenance HD at one of the enrolled units are eligible for inclusion in the study. Full lists of inclusion and exclusion criteria are included in Table 1.

**Table 1 Tab1:** Eligibility and Exclusion criteria

Eligibility Criteria	Exclusion Criteria
• Prevalent HD patient (> three months) • Aged 18 years or older • Able and willing to give informed consent	• unable to participate in current exercise programme due to perceived physical or psychological barriers • unable to undergo MRI scanning (metal implants, severe claustrophobia) • unfit to undertake exercise according to the American College of Sports Medicine (ACSM) guidelines

Patients will be recruited from centres within the East Midlands Renal Network, which cares for approximately 820 HD patients across four Counties in the United Kingdom. The three principal centres in Leicestershire care for around 350 patients. We anticipate 80 % will meet the inclusion criteria (320 patients). Conservatively assuming a 50 % consent/participation rate this will leave approximately 160 patients from which we will need to recruit 130.

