### Image analysis

All scans will be anonymised and analysed off-line blinded to patients’ data and treatment arm. CMR analysis will be both visual and quantitative following international recommendations [66]. Quantitative analysis will be performed by a single operator using FDA approved commercially available software. This will include: LV mass(g); End-diastolic volume (ml); end-systolic volume (ml); stroke volume (ml); and ejection fraction (%). All volumetric data will be indexed to body surface area.

T1 and T2 values will be taken from a mid-short axis slice of the LV by drawing epicardial and endocardial borders [49]. LV strain and strain rate will be assessed as previously described [44]. Endocardial and epicardial contours will be manually drawn onto the end-diastolic image and propagated and LV endocardial and epicardial circumferential and longitudinal strain and strain rates will be calculated.

Aortic distensibility will be analysed as previously described [67]. The ascending thoracic aortic area will be manually identified as a region of interest using JIM version 6 (Xinapse software, UK) and graphically represented against time. Aortic distensibility will be determined using the validated formula:$$ \left( maximum\  aortic\  area- minimum\  aortic\  area\right)/\left( minimum\  aortic\  area\kern0.5em X\kern0.5em \varDelta P\right) $$

ΔP is the brachial pulse pressure reading performed during CMR [68].

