#### Intervention: intradialytic exercise training

The intervention is a 6-month progressive intradialytic cycling programme. The intervention group will use specially adapted and calibrated exercise cycles (Letto series; Motomed, Reck, Germany, see Fig. 3) three times a week during dialysis, aiming for 30 min continuous cycling at a Rating of Perceived Exertion (RPE) of 12–14 [70] adjusting resistance as required to progress training (Fig. 3). Our pilot exercise programme of 31 patients has been well tolerated with no adverse symptoms reported in any of the exercising patients. It is accessible to patients of different ages, gender, cultures and ethnicities.

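### The exception that releases life-threatening imaging findings applies only to those seen during scan acquisition, so one first seen at the off-line reading is withheld until the patient finishes the study

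*Protocol article*

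**What the plan says.** Investigation reporting sets the rule: "Cardiac imaging will not be reported until after the patient has completed the study so as not to influence the study outcome". One exception follows: "However life-threatening incidental findings identified during scan acquisition will be reported to the chief investigator", the data safety management board and the sponsor. A full report is then issued, for the stated purpose of helping clinical care and keeping the patient safe.

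Image analysis describes what happens to the images next: "All scans will be anonymised and analysed off-line blinded to patients’ data and treatment arm". For cardiac MRI (CMR), that section plans both a visual and a quantitative assessment.

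Under Baseline assessments and Follow-up assessments, imaging is done at baseline and again at the end. The interim visit at month four has none: "This will involve all baseline assessments except the CMR, echocardiogram and NICOM". On the last visit: "Final assessments will be conducted for both exercise and control groups after seven months".

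**The concern.** The exception is limited twice. One limit is severity: the finding must be life-threatening. The other is the moment of detection: it must be noticed during acquisition. The first limit is a deliberate choice about how much clinical information to release. The second has no stated reason, and it does not fit the purpose given for the exception. A finding that is dangerous enough to release when the radiographer or sonographer sees it is no less dangerous when a reader sees it later.

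At stake is the safety of individual patients in either arm. If the off-line reading of a baseline scan takes place while the patient is still in follow-up, the trial could know of a life-threatening finding that its own rule tells it not to report. In the exercise arm that patient would meanwhile be cycling "three times a week during dialysis, aiming for 30 min continuous cycling".

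**Working it through.** The article gives no figure to reproduce on this point, and no sample-size or power formula applies. The check sets the sections side by side.

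1. **Default rule (Investigation reporting).** No cardiac imaging is reported before the patient completes the study. This is a positive instruction, so a finding not covered by the exception is withheld by rule and not merely left unmentioned.

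2. **Exception (Investigation reporting).** It covers "life-threatening incidental findings identified during scan acquisition will be reported". A finding must satisfy both conditions to qualify.

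3. **Later reading (Image analysis).** All scans are read off-line after anonymisation, and the CMR reading includes a visual assessment. Some results exist only after this step: volumes and ejection fraction come from drawn contours, and myocardial perfusion reserve (under Cardiac MRI) is a ratio calculated from rest and stress flow. Such results cannot meet an acquisition test, however serious they are.

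4. **Combining 1 to 3.**
   - Life-threatening, seen at acquisition: reported.
   - Life-threatening, first seen off-line: the default rule applies, so it is withheld.
   - Not life-threatening, whenever seen: withheld, as intended.

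   The second case is the gap. It differs from the first only in the time of detection.

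5. **How long it can last (Follow-up assessments).** Run-in of 1 month + 6 months of training = 7 months from baseline to final assessment. Intervention fidelity and monitoring adds missed sessions to the end of the period, so it can be longer. Month four has no CMR or echocardiogram, so no further main-study scan before the end could bring the finding under the exception. In practice the rule bears on the baseline scans.

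6. **Who is exposed (Sample size calculation).** The rule applies to every participant: 65 per group, 2 × 65 = 130. That is the number of patients under the rule, not an estimate of how many would have such a finding. The article gives no rate for that.

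7. **What is not determined.** Image analysis does not say when the off-line reading takes place. If baseline scans are read during follow-up, the gap is as described. If they are read only after the patient finishes, the clause withholds nothing known, because the images are simply unread until then.

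**The case against.** **The embargo is a defensible design choice.** This is right and stands. Its stated reason is to avoid influencing the outcome. In an open-label trial, a clinician who receives a patient's baseline LV mass or ejection fraction could change treatment and so move the primary endpoint. Blinded reading protects the measurement but cannot prevent that, so it would be wrong to say the blinding makes the embargo unnecessary. The embargo is not challenged here. The answer on the narrow point is that the article already accepts changed care as the price of releasing life-threatening findings. Releasing the same class of finding when it is seen later needs no new principle.

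**The full protocol may hold an incidental-findings procedure.** It may, and an article is not expected to reproduce one. But the point does not rest on silence: the article states a rule and an exception, and the exception is drawn too narrowly for its stated aim. If the full protocol already covers off-line findings, the article's wording should be aligned with it.

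**Other safeguards exist.** The one-month run-in, Holter recording with interim rhythm analysis, adverse event reporting and the data safety management board all remain in place. None of them is described as a route for a finding made at the off-line reading.

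**A stronger reading.** A reader might infer that the embargo contradicts the exclusion of patients "unfit to undertake exercise according to the American College of Sports Medicine (ACSM) guidelines", because the trial holds cardiac imaging while patients train. The article does not support this. Both provisions can be followed as written: nothing makes the study CMR or echocardiogram part of the fitness check, and whether the cited guidelines call for imaging cannot be judged from the article. The Background figure of LV hypertrophy in 75 % of dialysis patients does not help either. It describes the condition the trial hopes to reverse and says nothing about how often a scan would show unfitness.

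**Conclusion.** The point holds in a narrow form. As worded, the reporting rule withholds a life-threatening finding first noticed at the off-line reading until the patient completes the study, about seven months or more after baseline. The exception's own purpose gives no ground for treating it differently from the same finding seen during acquisition. This is a badly bounded rule with a patient-safety consequence and a cheap remedy.

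The conclusion assumes that at least some baseline scans are read off-line while the patient is still in follow-up, which the article neither states nor excludes. The number of patients affected is unknown and may be small. No contradiction with the fitness exclusion is shown, the general embargo remains justified, and the analysis of the primary outcome is not affected.

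**What to change.** Reconcile Investigation reporting with Image analysis by removing the words that tie the exception to scan acquisition. The route already described (chief investigator, data safety management board, sponsor, full report) would then apply whenever a life-threatening finding is seen. State that it applies identically in both arms, and add a step to re-link the anonymised scan to the patient. Having someone other than the image reader do the re-linking would keep the reader blind to identity and arm. The embargo on all other results and the blinded LV mass reading stay unchanged. Which findings count as life-threatening remains for the investigators, and no imaging-based fitness rule is proposed.

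The cost is a short amendment and a re-linking procedure, with no extra scans and no change to sample size or analysis. The downside is that a few patients' care may change during the trial, a cost the article already accepts for the same class of finding.

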### Image analysis

All scans will be anonymised and analysed off-line blinded to patients’ data and treatment arm. CMR analysis will be both visual and quantitative following international recommendations [66]. Quantitative analysis will be performed by a single operator using FDA approved commercially available software. This will include: LV mass(g); End-diastolic volume (ml); end-systolic volume (ml); stroke volume (ml); and ejection fraction (%). All volumetric data will be indexed to body surface area.

T1 and T2 values will be taken from a mid-short axis slice of the LV by drawing epicardial and endocardial borders [49]. LV strain and strain rate will be assessed as previously described [44]. Endocardial and epicardial contours will be manually drawn onto the end-diastolic image and propagated and LV endocardial and epicardial circumferential and longitudinal strain and strain rates will be calculated.

Aortic distensibility will be analysed as previously described [67]. The ascending thoracic aortic area will be manually identified as a region of interest using JIM version 6 (Xinapse software, UK) and graphically represented against time. Aortic distensibility will be determined using the validated formula:$$ \left( maximum\  aortic\  area- minimum\  aortic\  area\right)/\left( minimum\  aortic\  area\kern0.5em X\kern0.5em \varDelta P\right) $$

ΔP is the brachial pulse pressure reading performed during CMR [68].

#### ‘Usual care’: haemodialysis

Haemodialysis is a form of renal replacement therapy that replaces part of the excretory function of the kidneys by filtering waste, removing fluid and restoring electrolyte and acid-base balance by transferring blood from the body through a dialysis machine and returning it to the body. ‘Adequate’ dialysis is often assessed by calculating the clearance of small molecules during a dialysis session and guidelines for minimum suggested clearance exist [69]. This is only one measure of dialysis ‘adequacy’ however, and a dialysis machine only replaces certain aspects of renal function and patients receive a number of additional interventions as part of their ‘usual’ dialysis care. There are defined treatment targets for blood pressure, calcium, phosphate, haemoglobin and iron stores – including management of anaemia with erythropoietin stimulating agents (ESAs) and intravenous iron infusions [69] in addition to measures of adequacy from small molecule clearance. Both trial arms will continue ‘usual care’ aimed at achieving these targets to allow assessment of the effects of intradialytic exercise in addition to usual dialysis care.

#### Intervention: intradialytic exercise training

The intervention is a 6-month progressive intradialytic cycling programme. The intervention group will use specially adapted and calibrated exercise cycles (Letto series; Motomed, Reck, Germany, see Fig. 3) three times a week during dialysis, aiming for 30 min continuous cycling at a Rating of Perceived Exertion (RPE) of 12–14 [70] adjusting resistance as required to progress training (Fig. 3). Our pilot exercise programme of 31 patients has been well tolerated with no adverse symptoms reported in any of the exercising patients. It is accessible to patients of different ages, gender, cultures and ethnicities.

